### Intervention

The intervention is based on the daily use of the intervention footwear—Moleca®—for six months, for at least 42 hours per week (approximately six hours a day, seven days a week).

Moleca® footwear (Calçados Beira Rio S.A., Novo Hamburgo, RS, Brazil) is a low-cost women’s double canvas, flexible, flat, walking shoe without heels, with a 5-mm anti-slip rubber sole and a 3-mm internal wedge of ethylene vinyl acetate (Figure 2). Its mean weight is 0.172 ± 0.019 kg, ranging from 0.091 to 0.182 kg depending on the shoe size. This minimalist footwear has been produced on a large scale in Brazil since 1986 and is commonly worn by the elderly of lower social classes. We bought all the pairs of Moleca® shoes for the patients. For hygiene reasons, we ask the patients to wear thin cotton or silk socks with the footwear.

**Figure 2 F2:**
[figure not shown]
.** Moleca® shoes for women, made of double canvas, with flexible rubber soles and without heels.**

Every two weeks, the same physiotherapist (PT 1) makes phone calls to the IG patients in order to verify adherence to the treatment and the correct filling out of the diary. After three and six months of intervention, the patients in the IG group have their pair of Moleca® shoes photographed and checked for natural wear of the shoe with its daily use. If there are tears or holes in the shoes, they are replaced with a new pair.

During the intervention period, patients from the CG should not wear Moleca® or similar minimalist shoes, but they continue to receive their recommended health care and painkiller medication at the hospital. At the end of the intervention period, all CG patients also receive a free pair of Moleca® shoes.

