**Methods/Design:**

Fifty-six elderly women with knee OA grade 2 or 3 (Kellgren and Lawrence) are randomized into blocks and allocated to either the intervention group, which will use flexible, non-heeled shoes— Moleca®—for six months for at least six hours daily, or the control group, which could not use these shoes. Neither group is undergoing physical therapy treatment throughout the intervention period. Moleca® is a women’s double canvas, flexible, flat walking shoe without heels, with a 5-mm anti-slip rubber sole and a 3-mm internal wedge of ethylene vinyl acetate. Both groups will be followed for six months and will be assessed at baseline condition, after three months, and after six months (end of intervention). All the assessments will be performed by a physiotherapist that is blind to the group allocation. The primary outcome is the pain Western Ontario and McMaster Universities Osteoarthritis (WOMAC) score. The secondary outcomes are global WOMAC score; joint stiffness and disability WOMAC scores; knee pain with a visual analogue scale; walking distance in the six-minute walk test; Lequesne score; amount and frequency (number of days) of paracetamol (500 mg) intake over six months; knee adduction moment during gait; global medical assessment score; and global patient auto-assessment score. At baseline, all patients receive a diary to record the hours of daily use of the footwear intervention; every two weeks, the same physiotherapist makes phone calls to all patients in order to verify adherence to treatment. The statistical analysis will be based on intention-to-treat analysis, as well as general linear models of analysis of variance for repeated measure to detect treatment–time interactions (α = 5%).

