### Randomization and blinding

The randomization schedule was prepared using Clinstat software [26] by an independent researcher who was not aware of the numeric code for the control and intervention groups. A numeric block randomization sequence is kept in opaque envelopes.

After the patients’ agreement and assignment to participate in the research, the allocation into the groups is made by another independent researcher, who is also unaware of the codes. Only the physiotherapist responsible for the clinical trial knows who is receiving the intervention.

The initial and final clinical and medical examinations (Process A) are carried out by a rheumatologist who is blind to the patient’s allocation. One physical therapist (PT 2), who is blind to the treatment allocation, is responsible for all clinical, functional, and biomechanical assessments (Processes B and C). Another physical therapist (PT 1) is responsible for group allocation and monitoring the use of the intervention footwear by telephone. Both physiotherapists are blind to the block size used in the randomization procedure. The trial statistician is blind to treatment allocation until the main treatment analysis has been completed. To ensure that the researcher physiotherapists remain blind, they will emphasize to patients that they should not be told whether or not the patient has received the intervention footwear.

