### Protocol assessments

Eligible patients are assessed according to Process A, which consists of an interview and a clinical examination to classify the patient’s overall health condition, performed by the rheumatologist (global medical assessment score 1–5) and by the patient (global patient self-assessment score). Full-extension anterior–posterior knee radiographs are used to confirm the OA diagnosis and classification according to Kellgren–Lawrence criteria [23]. Process A is performed by a rheumatologist who is blind to the patient’s allocation. The two overall health condition assessments are conducted at baseline and at the end of the intervention period by the same physician.

At baseline, patients from both groups receive a diary to record the amount, in hours, of Moleca® use, and the intake of paracetamol tablets (500 mg) on a daily basis. Every three months, the diaries are collected in order to account for the Moleca® and painkillers use (Table 1).

**Table 1 T1:** Diary of intervention shoe use and Paracetamol intake

**NAME:____________________________________________________________________MONTH ** – First day:_____/_____/_____Final day: _____/_____/_____															
**DATE**	/	/	/	/	/	/	/	/	/	/	/	/	/	/	/

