**Secondary Outcomes**	
- Stiffness and disability subscale	- WOMAC osteoarthritis score
- Knee pain	- Visual Analogue Scale (0–10 cm)
- Function and progression of OA	- Lequesne’s algofunctional questionnaire score
- Six-minute walk test result	- Distance (m)
- Paracetamol (500 mg) intake	- Days and amount of paracetamol ingested over six months
- Knee load during gait	- Knee adduction moment (%body weight/height) by inverse dynamics during gait
- Global medical assessment	- Ordinal scale (1-much worse, 2-slightly worse, 3-no change, 4-slightly better, 5-much better)
- Global patient’s self-assessment	- Ordinal scale (1-much worse, 2-slightly worse, 3-no change, 4-slightly better, 5-much better)

The secondary outcomes are: total WOMAC score; joint stiffness and disability WOMAC subscale scores; knee pain symptom on movement, at rest, and at night with a VAS; walking distance in the six-minute walk test; Lequesne score; intake of paracetamol (500 gm) (number of days and quantity) over six months; knee load during gait; global medical assessment score; and global patient self-assessment score (Table 2).

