In this study, we highlight the crucial importance of periodic monitoring of the use of the intervention footwear and medication intake. One physical therapist has telephone contact with the participants every two weeks, to know about the use and the physical state of the intervention shoes, the filling out of the diary, and any issues related to the OA or medication intake. Usually, this practice is not observed in other studies [38,39] and may have interfered in their results. In these cited studies, the participants were asked only to record and return, via a packet sent in the mail, the number of hours they wore the study shoes per day, without monitoring regularly their usage.

Taking into account the period of daily use, we stipulated that the Moleca® shoe should be utilized for at least six hours daily, corresponding to 75% of the hours spent in usual daily activities. To determine this time usage, we took into account the analysis of van Raaij et al. [37], who determined the ideal timing of daily splint use, including insoles and braces, for knee OA. However, these same authors consider that the optimum amount of time for the use of the studied shoe cannot be categorically determined. Patients that have previously used Moleca® shoes for at least 25 hours weekly are excluded from this study in order to avoid bias in the results analysis.

The primary outcome measure is the pain WOMAC score, based on the OARSI task force [32]. This primary outcome, obtained by means of the WOMAC questionnaire, is widely used in the evaluation of knee OA. It is a valid, reliable, and responsive outcome measure that has been used as a main outcome in other randomized clinical trials in knee OA [39,40], and it is more sensitive to treatment changes than other WOMAC dimensions [28]. We used a linguistically validated Portuguese questionnaire [41].

Of our many secondary outcomes, we emphasize KAM. This variable is very important in representing knee loads during locomotion. In contrast to the other variables, which consist of subjective aspects, such as pain, stiffness, and disability, KAM is not subject to this drawback.

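### The article is inconsistent on whether controls receive the two-weekly calls; if they do not, the diary behind the paracetamol outcome is checked far more often in the shoe arm

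*Protocol article*

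**What the plan says.** Four places in the protocol article describe the telephone contact.

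- **Abstract, Methods/Design:** every two weeks "the same physiotherapist makes phone calls to all patients in order to verify adherence to treatment".
- **Intervention:** every two weeks PT 1 "makes phone calls to the IG patients in order to verify adherence to the treatment and the correct filling out of the diary". The section then covers inspection and replacement of the shoes. For controls it says that "patients from the CG should not wear" the study shoe or similar ones and that usual care and painkillers continue. It does not say whether controls are called.
- **Randomization and blinding:** PT 1 "is responsible for group allocation and monitoring the use of the intervention footwear by telephone". No arm is named.
- **Discussion:** "One physical therapist has telephone contact with the participants every two weeks". The topics listed are shoe use and shoe condition, diary completion, and problems with the disease or with medication.

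On the diary, the Protocol assessments section says that "patients from both groups receive a diary" for daily shoe hours and paracetamol tablets. It adds: "Every three months, the diaries are collected in order to account for the" use of shoe and painkillers. Table 2 lists as a secondary outcome "Days and amount of paracetamol ingested over six months". The Background gives reduced medication use as hypothesis (iv).

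**The concern.** The abstract and the Intervention section give different accounts of who is called, and both are current text. A therapist following the Intervention section could reasonably call the shoe arm alone.

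This matters because the call does more than support shoe wear. As the Intervention section describes it, the call also checks that the diary is completed properly, and the same diary holds the paracetamol record. A daily self-completed record may be kept differently by someone who is asked about it every fortnight than by someone who hands it in once a quarter. If the prompting differs by arm, part of any difference in recorded tablets or days could reflect recording rather than intake. Randomisation balances the women at entry. It does not balance how their outcome is collected afterwards.

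At stake is the interpretation of one secondary outcome and the hypothesis tied to it.

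**Working it through.** The article gives no figure to reproduce here. The check is a comparison of the texts, followed by a count of contacts.

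**Comparison of the texts**

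| Place | Who is called | Does it settle the matter? |
|---|---|---|
| Abstract | All patients | Explicit, but differs from the Intervention section |
| Intervention | Shoe arm named; controls not mentioned | No; it does not exclude controls |
| Randomization and blinding | No arm named; purpose is footwear monitoring | No |
| Discussion | Participants, no arm named | No; diary and medication topics fit both arms, shoe condition fits the shoe arm alone |

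**Inputs for the count**

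- Follow-up: six months, taken as 26 weeks (my conversion).
- Call interval: two weeks (abstract and Intervention).
- Diary collection: every three months, both arms (Protocol assessments).
- Controls: 28 (Sample size and statistical analysis).

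**Count per woman**

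- Calls: 26 / 2 = 13.
- Diary collections: 6 / 3 = 2.

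| Rule followed | Shoe arm | Control arm |
|---|---|---|
| Abstract: all called | 13 + 2 = 15 | 13 + 2 = 15 |
| Intervention text, controls not called | 13 + 2 = 15 | 0 + 2 = 2 |

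Under the second rule, the longest stretch between diary contacts is 2 × 7 = 14 days in the shoe arm and 26 × 7 / 2 = 91 days in the control arm.

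The 13th call would fall at week 26, together with the final collection. Without it there are 12 calls and 12 + 2 = 14 contacts, against 2. The contrast is essentially the same.

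**Calls needed to equalise the arms:** 28 × 13 = 364 at most.

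The count stops at contacts. The article gives nothing that converts a difference in contacts into a difference in recorded tablets.

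**The case against.** The strongest reply is that the two statements can be reconciled. The Intervention section never says that calls go to the shoe arm only. Its sentence stands in a passage on managing that arm, and calling those women is compatible with calling everyone. The abstract is explicit, and the Discussion's diary and medication topics apply to both groups. Even the footwear monitoring in the Randomization and blinding section makes sense for controls, who must avoid the shoe and whose diary has a line for its use. Both arms also have the same diary, the same written instruction and the same collection schedule.

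Much of this stands. A reader might infer that controls are not called, and hence that the paracetamol comparison is biased. The article supports neither step: silence about controls is not a statement that they get no calls, and unequal prompting would not by itself show which way recording moves, or how far. Nor does the point extend to WOMAC pain, which comes from a questionnaire given by the blinded assessor, PT 2, and not from the diary.

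The reply does not remove the inconsistency. The Methods section that should govern conduct names one arm, gives diary checking as a purpose of the call, and leaves controls out. The Discussion itself stresses regular monitoring of medication intake as well as shoe use, which is a reason to make the rule explicit for both arms.

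**Conclusion.** The point holds in conditional form. The article does not fix who receives the two-weekly calls, and one natural reading of its Methods text makes collection of a diary-based secondary outcome unequal: about 15 contacts against 2 per woman, with gaps of 14 days against about 91. On the abstract's reading there is no imbalance and only the wording is at fault.

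The figures rest on 26 weeks of follow-up, on calls made on schedule, and, for the unequal case, on controls receiving no calls. The effect on recorded paracetamol is unknown in size and direction. The matter should be corrected because the correction is cheap and hypothesis (iv) depends on the diary. It does not put the primary outcome in question.

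**What to change.** State in the Intervention section that PT 1 calls both groups every two weeks and asks the same questions about diary completion and paracetamol, with questions on shoe condition for the shoe arm alone. Bring the abstract, the Randomization and blinding section and the Discussion into line with that sentence.

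If all women are already called, the cost is a wording change. If not, it is at most about 364 short calls over the trial by the therapist who already makes them. Controls gain contact, but no more than the shoe arm has. PT 1 handles allocation and does not assess outcomes, so the blinding of PT 2 is unaffected.

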### Sample size and statistical analysis

The sample size calculation was made based on the achievement of a minimal clinically meaningful improvement [33] using an effect size of 0.30 (moderate effect size), considering the pain WOMAC score as primary outcome measure. We took the SD estimates from a study we had previously completed, in which we recruited a similar patient cohort [18]. A sample size of 56 patients is needed to provide 80% power to detect a moderate effect difference between the highest and lowest group pain means, assuming an alpha level of 0.05 and a statistical design of F test of repeated measures (between and within effects), and assuming a 10% loss to follow-up. Twenty-eight patients will be allocated to each group. The statistical analysis will be based on intention-to-treat analysis, and general linear models of analysis of variance for repeated measure will be used to detect treatment–time interactions (α = 5%). The outcome measures will be compared among baseline, three months, and six months, and between groups. The expected treatment effect is a difference of 20% between groups in the percentage of patients improved, using the WOMAC score [34].

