### Participants and recruitment

This study is currently recruiting patients (study start date: March 2011).

The eligibility criteria are:

Women 60 to 80 years of age

OA diagnosed according the American College of Rheumatology - ACR [22] criteria

Radiographic evidence of medial femorotibial classified as Kellgren–Lawrence [23] grade 2 or 3

Absence of diagnosed hip and/or ankle OA, rheumatoid arthritis, or systemic inflammatory arthritis; asymptomatic OA of both knees

Knee pain between 3 and 8 on a VAS

Body mass index (BMI) <35 kg/m^2^[17]

No history of surgical procedure on knee, ankle, or hip, and no muscle injury in the last six months

Absence of diagnosed neurological disease [24]

Leg length discrepancy smaller than 1 cm

Absence of rigid hallux [12]

Absence of arthroplasty and/or lower limb orthoses or indication of lower limb arthroplasty throughout the intervention period

Currently not using the Moleca® or similar shoes for more than 25 hours per week

No knee intra-articular steroid or hyaluronic acid three and six months, respectively, before inclusion in the study [12]

Absence of knee instability (verified by clinical examination to assess the collateral and cruciate ligaments)

Absence of dementia or inability to give consistent information [24]

Ability to walk independently without an assistive device for at least six hours a day

No physical therapy or acupuncture treatment throughout the intervention period

The use of paracetamol 500 mg every four hours is permitted for both groups for the control of pain, according to ACR recommendations for OA treatment [25]. NSAIDs and DMARDs are allowed if initiated at least eight and four weeks, respectively, prior to randomization, and they must be used in stable doses throughout the study [12].

The participants are recruited from three settings: (a) rheumatology clinic medical care located at the Hospital das Clínicas of the School of Medicine at the University of São Paulo, (b) orthopaedic ambulatory medical care located in the University Hospital, and (c) a primary care centre at the School of Medicine of the University. All potential patients are interviewed by telephone and, when selected, are assessed, in the rheumatology clinic of the Hospital das Clínicas of the School of Medicine at the University of São Paulo, by a rheumatologist who is blind to the patient’s allocation (Process A). The design and flowchart of the steps of the protocol are presented in Figure 1.

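### The plan promises intention-to-treat but names a repeated-measures ANOVA that, in its standard form, leaves out any patient with a missing visit

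*Protocol article*

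**What the plan says.** The section on sample size and statistical analysis puts the principle and the model in one sentence: "The statistical analysis will be based on intention-to-treat analysis, and general linear models of analysis of variance for repeated measure will be used". The stated purpose is to detect treatment-by-time interactions at a 5% level, and the abstract repeats the pairing. The same section fixes the visits: "The outcome measures will be compared among baseline, three months, and six months, and between groups". The primary outcome, WOMAC pain, is collected at all three (Protocol assessments, Process B).

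The plan expects incomplete follow-up. The 56 patients, 28 per group, were calculated "assuming a 10% loss to follow-up". The article does not say how a patient with a missing visit enters the model. It mentions no exclusion of such patients, no imputation and no mixed or likelihood-based model.

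**The concern.** A general-linear-model repeated-measures ANOVA is usually fitted to one row per patient with all visits filled. A woman seen at baseline and three months but not at six is then removed entirely, although two of her three scores exist. That conflicts with analysing all randomised patients in their assigned arms.

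What is at stake is bias. Patients know whether they were given shoes. Controls continue usual care and receive the shoes only at the end, so the reasons for leaving could differ by arm. If leaving also depends on how the knee feels, a comparison of completers no longer compares the groups as randomised.

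**Working it through.** **1. How many patients are affected.** Inputs from the article: 56 randomised, 10% loss. 56 × 0.90 = 50.4 complete and 56 × 0.10 = 5.6 incomplete, so about 5 or 6 women. Anyone who misses only the three-month visit adds to this.

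**2. The plan's own sample size.** Inputs: "using an effect size of 0.30 (moderate effect size), considering the pain WOMAC score as primary outcome measure", alpha 0.05, power 80%, two groups, m = 3 visits. The article does not name the effect-size metric or give the between-visit correlation ρ. I read 0.30 as Cohen's f and varied ρ. For the between-groups effect the noncentrality is λ = N f² m / [1 + (m − 1)ρ].
- At an assumed ρ = 0.3, N = 50 gives λ = 50 × 0.09 × 3 / 1.6 = 8.44 and power 81%. Then 50 / 0.90 = 55.6, rounded up to 56, which is the stated figure.
- Other correlations do not reproduce it. After inflation the total is 36 at ρ = 0, 49 at 0.2, 63 at 0.4 and 69 at 0.5.
- For the interaction, λ = N f² m / (1 − ρ) = 50 × 0.09 × 3 / 0.7 = 19.3 at ρ = 0.3, with power 98%.

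So 56 is attainable under one assumed correlation, with about 50 patients counted as evaluable. Under that assumption, losing 5 or 6 patients is already allowed for in the power.

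**3. Bias from analysing completers.** All of these inputs are assumptions: SD 1 at each visit, the same correlation r between all visits, a true difference in six-month change of 0.50 SD, and loss after month 3 among those with the worst three-month change.

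The three-month change has SD √[2(1 − r)]. The regression slope of six-month change on three-month change is (1 − r) / [2(1 − r)] = 0.5. If the worst fraction p of an arm leaves, the mean three-month change of those who stay moves by k(p) = φ(z) / (1 − p) standard deviations, where z cuts off the worst p. Hence

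completers' difference = 0.50 − 0.5 × √[2(1 − r)] × [k(control) − k(intervention)].

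Here k(0.20) = 0.350, k(0.14) = 0.259, k(0.07) = 0.144 and k(0) = 0. The SD of change is 1.183, 1.000 and 0.775 for r = 0.3, 0.5 and 0.7.

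| Loss, control / intervention | r = 0.3 | r = 0.5 | r = 0.7 |
|---|---|---|---|
| 10% / 10% | 0.50 | 0.50 | 0.50 |
| 14% / 7% | 0.43 | 0.44 | 0.46 |
| 20% / 0% | 0.29 | 0.33 | 0.36 |

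Simulated trials with 28 per arm agree. At r = 0.5 the completers' estimates were 0.496, 0.444 and 0.328 for the three rows, and a likelihood analysis of all observed data gave 0.495, 0.503 and 0.506.

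**4. Sensitivity to the assumptions.**
- If later visits are more alike (correlations 0.5 baseline to month 3, 0.7 month 3 to month 6, 0.4 baseline to month 6), the slope is 0.7 − 0.5 − 0.4 + 1 = 0.8. The 20%/0% case then gives 0.50 − 0.8 × 0.350 = 0.22.
- If poor responders are only more likely to leave, rather than certain to, the bias is smaller: 0.385 at 20%/0% and 0.467 at 14%/7% (r = 0.5).
- If the intervention arm loses more of its poor responders, the sign reverses and the benefit is inflated.

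**The case against.** A reader might infer that the primary result will be a completers' analysis. The documents do not support that. Nowhere do they say that incomplete patients are excluded, and intention-to-treat is stated twice. Imputation before the ANOVA would satisfy the text as written, and a condensed article may leave that rule to a fuller document. This stands, and it limits the point to what the named model does by default.

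A second objection is that not every ANOVA of this family deletes cases. A long-format version with a subject effect keeps the observed visits, and under equal correlations it removes the bias in step 3. This stands only in part. With correlations 0.5/0.7/0.4 that version implicitly uses a slope of 0.5 where the true one is 0.8, so the 20%/0% case still gives 0.50 − (0.8 − 0.5) × 0.350 = 0.40.

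Third, the dropout patterns are invented. Nothing in the article shows that loss will differ by arm, and the shoes promised to controls at the end may help retention. This stands: the table shows how large the bias could be and does not forecast it.

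Finally, a reader might infer from "No physical therapy or acupuncture treatment throughout the intervention period" and the similar arthroplasty criterion that randomised women would be removed for later treatment. The article has the physician apply the criteria after recruitment, as part of the baseline steps, and says nowhere that later events remove a patient. That reading does not hold.

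**Conclusion.** The point holds in a limited form. The named model, in its standard form, does not deliver the promised intention-to-treat analysis, and the plan's own 10% loss puts about 5 or 6 of 56 women at issue. Deletion is a default of the method and is not stated in the article.

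The size of any bias depends on the assumed dropout. There is none with equal, similarly caused loss. A true 0.50 SD becomes about 0.45 with a moderate imbalance and about 0.33 in an extreme one. Power is not the reason to act: it is 81% between groups and 98% for the interaction with 50 complete patients, at an assumed ρ of 0.3. The reason is that a better analysis is available at almost no cost and should be fixed before the data are unblinded.

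**What to change.** Name as the primary analysis a linear mixed model for repeated measures with treatment, visit and treatment-by-visit, an unstructured covariance and restricted maximum likelihood. It should use every observed visit of every randomised patient in her randomised arm. Alternatively, keep the ANOVA and state the imputation that brings all randomised patients into it.

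One clarifying sentence would also help: events after randomisation, such as starting physical therapy, do not remove a patient from the analysis of her arm.

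The change needs wording, standard software and a little more analysis work, with no new data or patients. The mixed model relies on data being missing at random given the observed scores, and the plan should state that assumption.

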Although it is reasonable to suppose a therapeutic effect of flexible, minimalist, and inexpensive shoes in the treatment of knee OA, its efficacy in reducing pain and KAM, as well as recovering musculoskeletal function in elderly people with knee OA has not been tested yet through a randomized, controlled trial. If effective, the use of these inexpensive, minimalist shoes might be part of a treatment prescription, representing a way of reducing costs associated with OA patients’ treatment.

Our hypothesis is that the use of the intervention footwear by elderly women with knee OA for at least six hours per day for six months could (i) relieve knee pain; (ii) improve musculoskeletal function in daily living activities; (iii) reduce knee load during gait; and (iv) reduce the use of medication, and, therefore, could be considered another inexpensive option for conservative OA treatment. Our aim is to investigate the therapeutic effect of inexpensive and minimalist footwear on the clinical and functional aspects of OA and gait biomechanics in elderly women with knee OA.

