### Outcome measures

The primary outcome measure is the pain WOMAC score (Table 2), based on the OARSI task force [32].

**Table 2 T2:** Outcome measures

**Primary Outcome**	**Measurement**
Pain subscale	WOMAC osteoarthritis score

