## Discussion

Based on our previous and promising results of an efficient reduction of knee joint load in women both with and without OA during activities of daily living using the same footwear [20,21], we propose a conservative and low-cost intervention for these patients. It is important to emphasize that this type of footwear has been available in our country on a large scale since the 1980s, and it is widely used for the comfort it provides. Therefore, it is expected that adherence to this form of therapy will be greater and easier than the use of knee braces [7,8] and subtalar strapping splints [9].

To our knowledge, this is the first randomized, clinical trial that aims at treatment for knee OA by means of inexpensive and minimalist footwear. We propose a flexible shoe as an intervention that mimics barefoot gait and, consequently, may reduce knees load in elderly women with chronic OA. If effective, at the end of the intervention, we expect to observe knee pain relief, improvement of musculoskeletal function in daily living activities, and reduced intake of analgesics by elderly women with knee OA.

In contrast to previous studies that include different levels of radiographic OA involvement [35-37], we emphasize herein the importance of selecting a more homogeneous group of patients, based on the Kellgren–Lawrence radiographic scale (grades 2 and 3). In fact, heterogeneity among radiographic involvement within the intervention and control groups could be associated with a variety of levels of symptoms and therefore, different effectiveness of the proposed intervention. Furthermore, only patients with pain in the 3–8 range of the VAS are included, in order to eliminate participants who probably will not achieve further improvement, as well as participants with more severe degrees of the disease, who probably will be less responsive.

Another issue taken into account was the higher BMI limit. In our study, the maximum permitted BMI was 35 km/m^2^. Although the KAM was normalized by a percentage of the subject’s body weight and height to allow for comparisons among subjects, high concentrations of fat in some parts of the body, such as the thigh and the pelvis, can provoke many movement artefacts and then interfere in KAM calculation.

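### The named test is a treatment-by-time interaction over three visits, while the question is pain at six months; no six-month contrast is designated as confirmatory, and power is usually, though not always, lost

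*Protocol article*

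**What the plan says.** In the protocol article, Sample size and statistical analysis, the only inferential procedure named is this: "general linear models of analysis of variance for repeated measure will be used to detect treatment–time interactions (α = 5" per cent). The Abstract repeats it. The next sentence gives the time levels: "The outcome measures will be compared among baseline, three months, and six months, and between groups". Baseline is therefore a level of the time factor. No model with baseline as a covariate is mentioned, and no visit or contrast is ranked above another.

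Outcome measures gives the primary outcome without a time point: "The primary outcome measure is the pain WOMAC score (Table 2), based on the OARSI task force".

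The question is tied to the end of treatment. The Background hypothesis concerns "the use of the intervention footwear by elderly women with knee OA for at least six hours per day for six months". The Discussion states the expected result: "at the end of the intervention, we expect to observe knee pain relief". The Abstract and the design overview both identify six months as the end of intervention.

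**The concern.** A two-group, three-visit interaction test asks whether the between-group difference changes anywhere across baseline, month 3 and month 6. The trial asks whether the groups differ in pain at month 6. The two can part company in either direction.

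- A difference at month 3 that has gone by month 6 makes the interaction true although the six-month hypothesis is false.
- A significant interaction gives no direction, size or interval for the end-of-treatment difference. The conclusion would then rest on a follow-up comparison that was not singled out beforehand.
- Spreading the test over 2 degrees of freedom, and using baseline as an outcome rather than a covariate, commonly costs power. With 28 patients per arm and 10% loss allowed for, there is little to spare.

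**Working it through.** **Inputs from the article (Sample size and statistical analysis).** 28 per arm; 10% loss, so 28 × 0.9 = 25.2, taken as 25 completers per arm; alpha 5%; power 80%; "using an effect size of 0.30 (moderate effect size), considering the pain WOMAC score as primary outcome measure".

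**Assumptions, not in the article.** The metric of 0.30 is unnamed. Read as Cohen's f with two equal groups, d = 2f = 0.60 SD. The SD is set to 1. The within-patient correlation r is varied. Errors have compound symmetry (equal correlation between visits) unless stated otherwise. The effect at months (0, 3, 6) is either full at both follow-up visits (0, 0.6, 0.6) or gradual (0, 0.3, 0.6).

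**The stated sample size.** The inputs given do not fix 56, because r and the metric are missing. Two readings reach it, each through 50 completers (50/0.9 = 55.6, rounded up to 56):

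- a between-groups F test with f = 0.30, three visits and r = 0.3, with noncentrality 0.09 × 50 × 3/(1 + 2 × 0.3) = 8.44 and power 81%;
- the omnibus interaction with d = 0.60 at both follow-up visits and r = 0.7.

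The standard interaction formula with f = 0.30 and three visits gives only 12 to 43 after loss, for r from 0.8 down to 0.

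**Formulas for the comparison, n = 25 per arm.**

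- Interaction, F on 2 and 96 df: λ = (n/2) × Σ(d_j − mean d)²/(1 − r).
  - Full effect at both visits: mean 0.4, sum of squares 0.16 + 0.04 + 0.04 = 0.24, so λ = 12.5 × 0.24/(1 − r) = 3.0/(1 − r).
  - Gradual effect: mean 0.3, sum of squares 0.09 + 0 + 0.09 = 0.18, so λ = 2.25/(1 − r).
- ANCOVA at month 6, F on 1 and 47 df: λ = (n/2) × d²/(1 − r²) = 12.5 × 0.36/(1 − r²) = 4.5/(1 − r²).

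| r | Interaction, full at both: λ, power | Interaction, gradual: λ, power | ANCOVA at month 6: λ, power |
|---|---|---|---|
| 0.3 | 4.29, 43% | 3.21, 33% | 4.95, 59% |
| 0.5 | 6.00, 57% | 4.50, 45% | 6.00, 67% |
| 0.7 | 10.00, 80% | 7.50, 67% | 8.82, 83% |
| 0.8 | 15.00, 94% | 11.25, 85% | 12.50, 93% |

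At r = 0.5 with the full effect at both visits, λ is 6.00 for both tests. The 10-point gap there comes from spending a second degree of freedom.

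**Serial correlation (simulation, AR(1)).** With the full effect at both visits and AR(1) 0.7, the interaction has 68% (65% with Greenhouse–Geisser correction) against 66% for ANCOVA. At AR(1) 0.8 it has about 85% (82% corrected) against 77%. With a gradual effect ANCOVA leads at both: 66% against 55% at AR(1) 0.7, and 77% against 71% at AR(1) 0.8.

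**Wrong-target check.** With an effect at month 3 only (0, 0.6, 0), the mean is 0.2 and the sum of squares is 0.04 + 0.16 + 0.04 = 0.24, so λ is again 3.0/(1 − r). The interaction is significant in 43%, 57% or 80% of trials at r = 0.3, 0.5 or 0.7. The six-month ANCOVA rejects in 5%, its nominal level.

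**The case against.** The strongest reply is that the article does provide for comparisons between groups across the three visits, which naturally takes in month 6. A difference confined to month 3 would be visible there. A reader might infer from the interaction wording that the trial cannot answer its six-month question; the text does not support that. What stands against the plan is narrower: the six-month comparison is one of several, and none is designated as confirmatory.

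A second reply is that this is a condensed article, and follow-up contrasts and covariates are commonly left to an analysis plan. That is fair as to omissions, and the article never uses the term primary test. But it does commit to the interaction at the 5% level, and that choice is what is questioned here.

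A third reply is that the interaction is a valid randomised comparison, so preferring ANCOVA is a matter of efficiency, and the efficiency claim rests on inputs the article does not give. This largely stands. A reader might infer that the interaction always loses power, or that the trial falls well short of its stated 80%. Neither follows. With d = 0.60 at both follow-up visits and r = 0.7, the interaction reaches 80% with exactly the stated 56 patients, and the loss against ANCOVA is about 3 points. At r of about 0.8, or under serial correlation, the advantage can vanish or reverse when the full effect is present at both visits.

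**Conclusion.** The point holds in two parts of different strength.

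**Target mismatch: high confidence.** The named test covers any change in the group difference over three visits. The hypothesis concerns month 6, and no six-month contrast is made decisive. This does not depend on the correlation. How often a month-3-only difference would make the interaction significant does: 43% to 80% for 0.60 SD and r from 0.3 to 0.7.

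**Power: moderate confidence.** With d = 0.60, 25 completers per arm and compound symmetry, ANCOVA gains 16, 10 and 3 points at r = 0.3, 0.5 and 0.7 if the effect is full at both visits, and about 25, 22 and 16 points if it is gradual. The gain is nil at about r = 0.8 in the first case and may reverse under serial correlation. The effect size, correlation and time profile are all assumptions.

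This should be changed, but it does not make the planned analysis invalid.

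**What to change.** Name one primary contrast: the between-group difference in WOMAC pain at six months, adjusted for baseline WOMAC pain. Estimate it by ANCOVA, or as the six-month contrast of a mixed model with baseline as a covariate. Report it with a 95% confidence interval and test it at 5%. Make the three-month contrast and the interaction secondary.

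Restate the sample size for that contrast, giving the SD, the correlation and the effect-size metric. The change of analysis does not by itself secure 80% power: under the assumptions above, ANCOVA needs 92, 76 or 54 patients in total after 10% loss at r = 0.3, 0.5 or 0.7.

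The cost is wording in the protocol or analysis plan, since baseline WOMAC pain is already collected. The downside is small: an effect seen only at month 3 would no longer count as a positive primary result, and a little power could be lost if the within-patient correlation is very high.
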